### 6.2.2 Biomechanics modelling and simulation

#### *Experimental data*

Anthropometric parameters required for scaling the biomechanical model are obtained from the participants. Participants are fitted with 39 reflective markers. A static standing calibration and functional calibration movements for the hip joint centre (star-arc) and knee joint axis (half squat) are first performed. Then the participants perform walking with self-select walking speed and forward lunges in the motion capture laboratory. The instruction in the forward lunge is to take a long step forward, go down to 90 degrees of knee flexion and return to the standing posture as fast as possible. During the movements marker trajectories (100 Hz, Vicon Motion Systems Ltd, UK) and ground reaction forces (1000 Hz, OR-6, Advanced Mechanical Technology Inc., USA) will be recorded. Gaps in the marker trajectories are filled and marker trajectories and ground reaction forces data are low-pass filtered (recursive 4th order low-pass Butterworth filter with 6Hz cut-off frequency). Six walking trials all within  $\pm 0.1$  km/h and three forward lunges are selected for further analysis using musculoskeletal modelling and simulation.

#### *Musculoskeletal modelling and simulation*

Musculoskeletal modelling simulation is performed in OpenSim software. A musculoskeletal model designed for analysis of movement with large hip and knee joint excursions is used. The model is further modified to improve knee extensor muscle moment arm at large knee flexion angles and to account for autograft donor muscle impairment by adjusting semitendinosus and gracilis muscle optimal fibre length and maximal isometric muscle force as per Saxby et al. (2016). Then, the model is scaled to match the mass and dimensions of the participant based on the measured body mass and marker locations from a standing calibration trial. The estimated hip joint centre and knee joint axis are used to assist scaling of the pelvis, femur, and tibia segments and subsequently to locate joint centres. The maximum isometric force of the knee extensor and flexor muscles are scaled to match experimentally measured knee extension and flexion strength, respectively. In all other muscles, it is assumed that the muscle strength scales relative to the body mass of the participants. Joint kinematics are calculated using inverse kinematics algorithm in OpenSim followed by inverse dynamics to calculate intersegmental resultant forces and moments. Static optimization is used to estimate muscle forces while accounting for muscle force-length properties with a cost function minimizing the sum of squared muscle activations. Finally, a joint reaction analysis tool is used to estimate knee joint contact forces. The simulations are performed for the ground contact phase of walking and forward lunge.

The biomechanical outcomes are means of six successful walking trials/three successful forward lunge trials. The outcomes of the walking trials (peak knee extensor moment, peak quadriceps muscle force, peak knee joint contact force, peak knee flexion angle) are extracted from the 1st half of the stance phase. We focus on the 1st half of the stance phase since in this phase it is the knee extensor muscles that are controlling the knee flexion and are the main contributors of the compressive forces at the tibiofemoral joint. Later in the stance, the main contributor to the compressive force is gastrocnemius muscles. Regarding the forward lunge trials these outcomes are extracted across the whole foot-ground contact phase. The peak knee extensor moment, peak quadriceps muscle force, peak knee joint contact force outcomes will be normalized to body mass; moments are expressed as Nm/kg and forces as N/kg.

## STATISTICAL ANALYSIS PLAN: MIRAKOS

The walking speed is assessed by photocells during each individual walking trial and calculated as the mean walking speed (m/s) of the six walking trials selected for further biomechanical analysis.

The forward lunge foot-ground contact time is assessed as the time in s where the foot is in contact with the force plate during the lunge movement. The vertical ground reaction force signal is used to detect this period. The foot is considered to be in contact with the ground when the ground reaction force signal is above 10 N. The forward lunge foot-ground contact time outcome is calculated as the mean of the three forward lunge trials selected for the biomechanical analyses.

### **6.2.3 KOOS**

The Knee injury and Osteoarthritis Outcome Score (KOOS), a disease-specific instrument, is an extension of the Western Ontario and McMaster Universities Osteoarthritis Index (WOMAC). The KOOS consists of 42 items covering five domains, namely, Pain (9 items), Symptoms (7 items), Activities of Daily Living (ADL) (17 items), Sports and Recreation (5 items), and knee-related QoL (4 items). The KOOS adopts a five-point Likert scale scoring system (ranging from 0 (least severe) to 4 (most severe)). A normalized score is calculated for each domain with 100 indicating no symptoms and functional impairment and 0 indicating extreme symptoms and functional impairment. In accordance with the user guide (<http://www.koos.nu>), if the number of missing items is less than or equal to 2 in a subscale, they will be substituted by the average item value for that subscale. If more than two items of the subscale are omitted, the response will be considered invalid, and no subscale score calculated.

### **6.2.4 The International Knee Documentation Committee (IKDC questionnaire)**

The IKDC questionnaire is an instrument to assess patients with a variety of knee disorders including ligamentous and meniscal injuries as well as patellofemoral pain and osteoarthritis. The questionnaire consists of three subscales: symptoms (7 items), sports activity (2 items), and knee function (2 items) and provides an overall function score. The scores are obtained by summing the individual items and then converting the crude total to a scaled number that ranges from 0 to 100. This final number represents a measure of function with higher scores representing higher levels of function. Thus, a score of 100 reflects no functional limitations. The IKDC score may be calculated if there are missing data, providing that responses have been given for at least 90% of the items. To calculate the IKDC score in case data are missing, the average score of the items that have been answered will be used to substitute for the missing item score(s). In case responses are missing for more than 90% of the items the IKDC response will be considered invalid.

### **6.2.5 Intermittent and Constant Osteoarthritis Pain questionnaire (ICOAP)**

The ICOAP is a diagnosis-specific 11-item questionnaire designed to assess the pain experienced within the last week among people suffering from knee and hip OA. The questionnaire is divided into two domains, a 5-item scale for constant pain and a 6-item scale for intermittent pain (so-called “pain that comes and goes”). Each domain captures pain intensity as well as related distress and the impact of OA pain on quality of life. All items are scored on anchored rating scales with five levels of response (0–4). The ICOAP outcomes comprise the two subscales 1) the constant pain subscale (0–20) and 2) the intermittent pain subscale (0–24), and the total pain score (0–44). Normalized scores for the two subscales and the total pain score, from 0 (best) to 100 (worst), are calculated. If there are three or more items missing, the response is considered invalid. If there are less than 3 items missing,

## STATISTICAL ANALYSIS PLAN: MIRAKOS

the missing item can be replaced with the mean of the responses to other items within the same sub-scale.

### **6.2.6 Tegner score**

The Tegner activity scale is an instrument to measure activity following knee injuries. It grades activity based on work and sports activities on a scale of 0 to 10 one-item scores. Zero represents disability due to knee problems and 10 represents competitive sports (e.g., soccer - national and international elite level). The subjects report the level of participation that best describes their current level of activity and that before the injury. The change in Tegner score is calculated as the difference between the current activity level Tegner score and pre-injury activity level Tegner score. Negative values will indicate a decline in the activity level.

### **6.2.7 Pressure pain sensitivity**

The pain sensitivity will be assessed by computerised cuff pressure algometry (CPA). A double-chambered Tourniquet cuff is wrapped around the calf by the gastrocnemius muscles of the lower extremity of the ACL reconstructed leg. A computer-controlled compressor inflates the cuff with air at 1 kPa/s. The participant is asked to indicate the first sensation of pain on the handheld device with a slider by moving the slider upwards (lowest level indicate no pain, highest level indicate worst imaginable pain). The inflation continues until the participant presses the stop button on the handheld device. The pressure pain sensitivity is assessed by two pressure pain thresholds: the pressure pain detection threshold (PDT) and the pressure pain tolerance threshold (PTT). The PDT defines the pressure where the pain is detected (i.e., the first time the participant moves the slider away from zero) and PTT defines the pressure, at which the pain becomes intolerable (i.e., where the participant presses the stop button). The recorded pressures are measured in kPa. The test is repeated four times separated by resting periods of 3 minutes. The first measurement is used for familiarization and the following three are used for the analysis. The PDT and PTT outcomes are calculated as means of the three measurements.

### **6.2.8 The radiographic knee OA level**

The evaluation of radiographic signs of knee OA is done according to Kellgren-Lawrence grading at Frederiksberg Hospital by the same highly experienced rheumatologist. Scores on the Kellgren-Lawrence scale range from 0 to 4, with a score of 2, 3, or 4 indicating definite osteoarthritis and higher scores indicating more severe disease.

### **6.2.9 Knee pain during movement/muscle strength tests**

The current knee pain during the muscle strength, walking and forward lunge tests will be assessed by a VRS 0-10 immediately after each trial, where 0 indicates 'no pain at all' and 10 indicates 'worst imaginable pain'. The knee pain will be calculated as the mean VRS reported during the trials selected for further analysis (for walking this is six and for forward lunge/muscle strength, it is three trials).

### **6.2.10 Knee joint laxity**

Instrumented knee joint laxity testing will be measured using a digital arthrometer (Lachmeter, Lachmeter Company Equipamentos Ortopedicos LTDA, Ribeirao Preto, Brazil). This quantifies the anterior translation of the tibia relative to the femur. The participant is lying supine on an examination table with a wedge cushion behind the thigh ensuring the same degree of knee flexion for all measurements. The participant is asked to relax the thigh muscles and especially the hamstrings during the

---

 [https://oarsi.org/sites/default/files/docs/2013/icoap\\_users\\_guide\\_07072010.pdf](https://oarsi.org/sites/default/files/docs/2013/icoap_users_guide_07072010.pdf)

## STATISTICAL ANALYSIS PLAN: MIRAKOS

test. The knee joint laxity will be assessed three times for each knee. The mean of the three assessments for each leg are calculated and the knee joint laxity side-to-side difference will be calculated by subtracting the mean knee joint laxity of the contralateral knee from the mean knee joint laxity of the ACL-reconstructed knee. The unit of this variable is mm. The knee joint laxity is included in the participant characteristics (Table 2).

### 6.3 STATISTICAL ANALYSIS METHODS

#### 6.3.1 Primary analysis

The primary analysis applied for estimation of between-group differences of all selected outcomes (section 6.1) will be an analysis of covariance (ANCOVA) for continuous data. The results will be reported as mean  $\pm$  SD, mean differences with 95% confidence interval (CI) and the level of significance is set to 0.05.

Categorical data and counts (percentages) will be analysed using Chi-square statistics comparing distributions between groups.

Binary data will be presented as risk differences with 95% CI.

The results of the analyses will be presented in tables that resemble the Tables 2-4 shown in section 9.0.

### 6.4 MISSING DATA

#### 6.4.1 Reasons for missing data

Missing data may potentially occur due to technical issues, electrical power supply breakdown, or other unforeseen issues related to the test equipment. If this should happen the missing data will be considered as missing completely at random.

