#### 7.4.2 Forward lunge biomechanics

The participants will be instructed to perform forward lunge movements at maximal pace ("as fast as possible"). The forward lunge movements are performed by taking one step forward, placing the foot on the force plate, flexing the knee to  $90^\circ$  and subsequently push backwards into the starting position, while having hands on the back of the head, the upper body perpendicular to the ground, and the opposite foot maintaining ground contact. Three forward lunge movements will be recorded with a short resting period ( $\sim 60$  s) in between.

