### 3.2 SAMPLE SIZE, POWER AND DETECTABLE DIFFERENCE

We will compare the quadriceps muscle strength between two groups of ACL reconstructed individuals: 1) symptomatic and 2) asymptomatic.

The variance in this population is unknown, while our sample size estimation will be pragmatic. To detect a group difference of 0.3 Nm/kg in the primary outcome with a common standard deviation of 0.5 Nm/kg, a sample size of 50 per group will have a power of 84%, ( $\alpha = 0.05$ ). Thus, a total sample size of  $n=100$  (50/50 per group) was originally intended to be applied. However, in November 2021 71 (17/54 symptomatic/asymptomatic) participants were recruited and included in the study, indicating a low prevalence of symptomatic participants. We estimated that it would be difficult to recruit

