### 4.2 STATISTICAL SIGNIFICANCE AND CONFIDENCE INTERVALS

A P-value  $< 0.05$  are considered statistically significant for our primary outcome. Results will be reported as mean values with standard deviation (SD), or group mean differences with a 95% confidence interval (CI).

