#### 6.1.3 Key secondary outcomes

The following outcomes are assessed as key secondary outcomes:

- The peak knee extensor moment during walking defined as the mean of the individual peak knee extensor moment values across six walking trials. The unit for this outcome is Nm/kg (section 6.2.2).
- The peak knee extensor moment during the forward lunge defined as the mean of the individual peak knee extensor moment values across three forward lunge trials. The unit for this outcome is Nm/kg (section 6.2.2).
- The peak quadriceps muscle force during walking defined as the mean of the individual peak quadriceps muscle force values across six walking trials. The unit for this outcome is N/kg (section 6.2.2).
- The peak quadriceps muscle force during the forward lunge defined as the mean of the individual peak quadriceps muscle force values across three forward lunge trials. The unit for this outcome is N/kg (section 6.2.2).
- The peak knee joint contact force during walking defined as the mean of the individual peak knee joint contact force values across six walking trials. The unit for this outcome is N/kg (section 6.2.2).
- The peak knee joint contact force during the forward lunge defined as the mean of the individual peak knee joint contact force values across three forward lunge trials. The unit for this outcome is N/kg (section 6.2.2).

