#### 6.4.2 Imputation method

In case, a given variable has more than 10% missing data, multiple imputation will be applied. All the existing data of that variable will be used to predict the missing values.

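### SAP 6.4 has no rule for strength or lunge tests missing or incomplete because of knee pain; if such gaps occur, the planned handling could shrink the group difference

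*Combined protocol and SAP*

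**What the plan says.** SAP 6.4.1 lists possible reasons for missing data. All concern the equipment or its power supply. Of these it says: "If this should happen the missing data will be considered as missing completely at random".

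SAP 6.4.2 is not limited to any cause: "In case, a given variable has more than 10% missing data, multiple imputation will be applied". The prediction is to use the available values of the same variable. Neither group nor pain score is named as a predictor, and no method is given at or below 10%.

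The tests are demanding. Protocol 7.4.2 states: "The participants will be instructed to perform forward lunge movements at maximal pace", with the knee flexed to 90°. SAP 6.2.1 asks for maximal effort in the strength test. SAP 5.2 defines the symptomatic group by a pain score of at least 3 in the reconstructed knee.

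The outcomes differ in what they need. SAP 6.1.3 defines the lunge moment as the "mean of the individual peak knee extensor moment values across three forward lunge trials"; lunge quadriceps force and contact force follow the same pattern, and SAP 6.2.2 requires the trials to be successful. The primary (SAP 6.1.2) is the single highest torque among three contractions. SAP 5.4 expects withdrawal to be negligible and gives no analysis rule for a consented participant who cannot do the experiments.

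**The concern.** In a group selected for knee pain, the foreseeable reason for an undone or unfinished maximal test is that pain. SAP section 7.0 itself argues that knee pain reduces quadriceps activation and force, so participants who cannot perform would plausibly be among the weaker ones. Analysing completers only, or filling gaps from completers' values, treats them as similar to those who performed. That would raise the symptomatic mean and work against both hypotheses.

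The SAP also does not say whether a participant with one or two successful lunges has an outcome. A missing strength test could spread further, because SAP 6.2.2 scales the model's knee muscles to measured strength, which feeds the quadriceps-force and contact-force outcomes.

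**Working it through.** **Inputs.** SAP 3.2: "To detect a group difference of 0.3 Nm/kg in the primary outcome with a common standard deviation of 0.5 Nm/kg"; 30 symptomatic and 90 asymptomatic; stated power 80.6% (84% for the original 50/50). SAP 6.3.1: "the level of significance is set to 0.05". Sidedness is not stated. The number of pain-related missing tests is not in the documents, so 3 to 12 of 30 symptomatic is an assumed range.

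**1. The plan's own figure.** Two-sample t-test, noncentrality = 0.3 / (0.5 × √(1/30 + 1/90)) = 2.846, 118 degrees of freedom, two-sided: power 80.59%, matching 80.6%. For 50/50 the noncentrality is 3.0 and power 84.39%, matching 84%. One-sided power would be 88.2% and 90.9%, so the plan used two-sided tests. There is no allowance for missing data.

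**2. The 10% trigger.** It counts both groups together: 10% of 120 = 12, which is not more than 10%. So 12 values can be missing with no method stated. If all 12 were symptomatic, that is 12/30 = 40% of that group.

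**3. Completers only.** If a fraction q of the symptomatic group is missing, and missingness correlates ρ with low strength, the symptomatic mean rises by ρ × SD × φ(z_q)/(1 − q). The factor φ(z_q)/(1 − q) is 0.195 at q = 0.10, 0.350 at 0.20 and 0.644 at 0.40. At q = 0.10 and ρ = 1 the expected difference is 0.3 − 0.5 × 0.195 = 0.20 Nm/kg. The formula is for a large population. Simulation with groups of 30 and 90 (20,000 runs per case) gives slightly smaller shifts, as expected when the weakest are drawn from only 30:

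| Missing of 30 | Expected difference, ρ = 0.5 | ρ = 1 (weakest missing) | Power, ρ = 0.5 | Power, ρ = 1 |
|---|---|---|---|---|
| 3 | 0.25 | 0.21 | 64% | 50% |
| 6 | 0.22 | 0.13 | 48% | 22% |
| 12 | 0.15 | about 0 | 20% | 4% |

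At ρ = 0 the expected difference stays 0.30 and only power falls: 77%, 74% and 63% for 3, 6 and 12 missing.

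**4. Above the trigger.** Take 13 symptomatic values missing (13/120 = 10.8%), set the asymptomatic mean to 0 and the true symptomatic mean to −0.3.

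- *Missing participants no weaker, imputed from both groups pooled.* Observed mean = 17 × (−0.3)/107 = −0.048. Completed symptomatic mean = (17 × (−0.3) + 13 × (−0.048))/30 = −0.19, so the difference shrinks to 0.19. Imputing within group keeps 0.30.
- *Missing participants 0.5 Nm/kg weaker than completers.* Observed symptomatic mean = −0.3 + (13/30) × 0.5 = −0.083. Within-group imputation gives 0.08; pooled imputation gives 0.05.

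The SAP does not say which reading applies. If the missing are weaker, neither recovers 0.30.

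**5. Lunge outcomes.** No planned difference or SD is given, so the direction can be argued but the size cannot be computed.

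**The case against.** A reader might infer that the SAP assumes pain-related gaps are missing completely at random. It does not. That sentence refers to equipment faults, for which it is reasonable; on pain the SAP is silent.

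A reader might also infer that symptomatic participants will drop out and that the group will look better than it is. No count supports this. Participants pass a clinical examination, BMI is capped at 30, known full-thickness cartilage lesions are excluded, and withdrawal is expected to be negligible. Pain may mostly lower performance rather than prevent it, and the plan captures that: the primary needs only one good contraction, lunge contact time and peak knee flexion are outcomes, pain is rated after every trial (SAP 6.2.9), and the flow diagram will show withdrawals. The SAP also calls its analyses exploratory.

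These points make the risk conditional and lighten it for the primary. They do not fill the gap. The expected withdrawal rate concerns leaving the study, not failing one test, and the flow diagram need not show a single skipped test. SAP 6.4.2 would still apply to a pain-related gap as it does to any other.

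Assigning non-performers the lowest observed value would favour the study's own hypotheses by construction. It is also ill-defined for joint contact force, where the SAP itself calls the causal evidence linking loading to osteoarthritis weak. That objection stands and limits such an analysis to an extreme bound.

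**Conclusion.** The gap is real, and its effect is conditional. If tests are missing or incomplete because of pain, and those affected are weaker than the rest of their group, the rule as written could bias the difference towards zero. The exposure lies mainly in the three lunge key secondary outcomes and less in the primary.

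On the primary's planning values, 3 of 30 missing would turn 0.30 Nm/kg into about 0.25 to 0.21. This assumes that all losses are symptomatic, that completers only are analysed, and that ρ is 0.5 to 1. With ρ = 0 there is no bias.

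The 12-of-30 case, where the whole difference can vanish, needs every missing value to be symptomatic and those participants to be the weakest. It is an extreme bound, not a forecast. The percentages cannot be carried over to the lunge outcomes. The SAP should be amended.

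**What to change.** Amend SAP 6.4 as follows.

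1. Limit the missing-completely-at-random assumption to technical causes, and classify each missing or failed test as technical or as pain/inability. For participants already measured (71 were included by November 2021), use existing test records.
2. Compute walking and lunge outcomes from the valid trials obtained, with at least one required.
3. Report the number unable because of pain in each group as a risk difference with 95% CI, a format SAP 6.3.1 already provides. Zero is also worth reporting.
4. State the handling at or below 10% missing. If imputation is used, include group and the pain scores in the model.
5. Add a sensitivity analysis for data not missing at random, for the primary and lunge outcomes, over a range of shifts. For the primary, 0, 0.25, 0.5 and 0.75 Nm/kg would serve as an example; since bias = fraction missing × shift, 3 of 30 at 0.5 gives 0.05 Nm/kg. For lunge outcomes, express shifts in observed SDs. Use lowest observed value or worst rank only as an extreme bound, and only where the worse direction is clear.

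The cost is one record field, a look back through existing records, some SAP wording and one added analysis. A mean of one or two trials is noisier than a mean of three, and reasons recovered from old records may be incomplete.
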